## Abstract

**Background:**

In Uganda, 22% of all women of reproductive age have an unmet need for family planning services. Access to contraceptive services, especially long-term reversible contraceptives such as implants, remains a challenge. The number of trained health providers is also not sufficient to address the needs for contraception. The Uganda Ministry of Health implemented a community-based implant provision pilot project where community health extension workers (CHEWs) were trained and accredited to insert implants at community level.

**Objective:**

This study aims to evaluate the implementation and acceptability of stakeholders toward task shifting the provision of family planning implants to CHEWs in Uganda.

**Methods:**

The evaluation will use a cross-sectional design using both quantitative and qualitative methods. The quantitative component will use a noninferiority design, whereas the qualitative component will use a descriptive approach. The noninferiority design involves a comparison of the competence of the currently authorized cadre to offer the service to the proposed cadre (CHEWs). Compared with a randomized controlled trial, the noninferiority design is more appropriate for this evaluation because the CHEWs and the authorized cadre are not comparable in terms of level of training and competencies. The authorized cadre has gone through formal training, which is not comparable with the training the CHEWs have received, and so the comparison is such that the competencies of the CHEWs are noninferior or at most equal to the competencies of the authorized cadre. Quantitative data will be collected among 92 CHEWs and 92 qualified health workers using performance assessment checklists and practice-based questionnaires that were developed based on the training manuals. Competency will be measured on a continuous scale and summarized as mean (SD) scores. Qualitative data will be collected through key informant interviews (n=23), in-depth interviews (n=24), and focus group discussions (n=18). Qualitative data will be analyzed using thematic analysis following the framework method for the analysis of qualitative data using ATLAS.ti (version 9).

**Results:**

Preliminary findings indicate improved confidence and capacity of community health workers to provide implants despite challenges such as poor waste disposal, record keeping, and data management. By August 2025, training of research assistants had been concluded, and data collection had started. We anticipate that the data collection will be completed by the end of October 2025, the data analysis will be completed by November 2025, and the final results will be published by December 2026.

**Conclusions:**

This pilot will generate contextual information that can be used to improve access to family planning services at the community level.

## Introduction

### Background

The Sustainable Development Goals target 3.7 aimed to achieve 75% of the global demand for contraception by 2030 [1,2]. However, many women of reproductive age might never get access to quality contraceptive services and commodities for reasons such as insufficient information about available methods, stigma [3], shortage of family planning commodities, and few adequately trained health providers. A modeling study estimated that the global prevalence of modern contraceptive use among 1.9 billion women of reproductive age increased from approximately 55.0% in 2000 to 57.1% in 2019 [4]. However, the study also noted that approximately 164 million women of reproductive age still face unmet need for family planning and that Sub-Saharan Africa experiences a disproportionately higher proportion of women with an unmet need for family planning (23.1% [5]) compared with other regions such as Asia and Latin America, where the unmet need is approximately 10% [4].

In many low- and middle-income countries, the number of trained health providers is not sufficient to address the need for contraception [6,7]. In addition, less than half of the available trained health workers serve rural areas, where a significant proportion of the population resides [7,8]. To address this challenge, the World Health Organization acknowledges task shifting as an innovative approach to promote and accelerate equitable access to care, especially in low- and middle-income countries. It is defined as “the rational redistribution of tasks among health workforce teams,” where tasks are moved, transferred, or delegated, as appropriate, from trained and qualified health workers to other health workers with shorter training and fewer qualifications [8], to make more efficient use of the available human resources for health and improve service access.

In 2010, Uganda developed ambitious goals and targets for the transformation of its people and the achievement of a modern and prosperous society as per Vision 2040. Between 2010 and 2040, the country aimed to reduce the maternal mortality rate from 336 to 15 deaths per 100,000 live births, increase modern contraceptive prevalence rates from 35% in 2016 to 50% in 2030, and reduce unmet need for family planning from 28% in 2016 to 10% by 2030 [9]. To achieve these targets, various strategies have been instituted, including scaling up self-care and task shifting through engaging community health extension workers (CHEWs) to support service access and increase family planning uptake at the community level.

### Community-Based Implant Provision Project

The Uganda Ministry of Health developed a CHEWs strategy to support the achievement of the ambitious Vision 2040 and the 2030 Sustainable Development Goals targets. The objective of the strategy is to competently train and launch a cadre of health care providers, known as CHEWs, to deliver quality, preventive, promotive, and selected basic curative health services at the community level, including providing contraceptives.

The Uganda Ministry of Health implemented a pilot community-based implant project, which involved training CHEWs to provide long-acting reversible contraceptives. Specifically, CHEWs were trained to insert family planning implants and refer clients who needed services of removing the implants to health facilities. This approach has previously been tested in Ethiopia [10] and Nigeria [11]. However, there is a need to generate context-relevant evidence in Uganda to support the community-level provision of implants, even as global health stakeholders advance task shifting and sharing [12,13], community-based service delivery, and self-care for sexual and reproductive health.

The community-based implant provision project was piloted in Lira City, Kyotera, and Namutumba districts in Uganda. All CHEWs in the aforementioned districts underwent additional training specific to family planning focused on implant insertion. The additional training focused on implant provision and was designed to equip the CHEWs with knowledge, skills, and clinical competencies to provide Implanon NXT (Organon Pharma Limited) insertion as well as appropriate referral for implant removal. The training on implant insertion was provided for 8 days, with 4 days of classroom-based learning and 4 days of facility-based practicum. The training was delivered by national-level trainers using a training manual developed by the Uganda Ministry of Health. After successful training, the CHEWs were accredited and deployed at their immediately supervising health facility to conduct implant insertion services. By the end of the training, the CHEWs were expected to have acquired knowledge and demonstrate the following clinical competencies: (1) provide effective client counseling sessions addressing concerns and misconceptions, for informed choice and obtain consent from at least 3 to 5 women, (2) perform comprehensive client screening and medical eligibility for Implanon NXT, (3) prepare the insertion site, (4) perform Implanon NXT insertion in 5 clients using correct techniques, (5) provide clear postinsertion care instructions to 5 clients, (6) manage clients with family planning–related side effects and provide appropriate referral pathways (optional), (7) accurately and appropriately record the family planning services provided in family planning registers and client cards (5 records), and (8) maintain a safe and sterile environment during 5 procedures.

The project was facility-based, whereby CHEWs were stationed at their supervising facilities within their communities. During the duration of the intervention, the CHEWs worked alongside and were supervised by health workers to offer Implant NXT contraception to any woman who required it, was eligible, and consented. The CHEWs were then accredited to offer the services independently.

### General Objective

The overall objective is to evaluate the implementation of a community-based implant intervention to inform efforts aimed at task shifting the provision of long-term reversible family planning methods in Uganda.

### Specific Objectives

The specific objectives of the study are to (1) explore the perceptions of the stakeholders toward implant provision task shifting to the CHEWs (stakeholders including the CHEWs, clients, health workers or professionals, and policymakers), (2) assess the acceptability of the community-based implant insertion by CHEWs among the stakeholders (health workers at the facility and family planning clients in the community), and (3) determine the competence of the CHEWs regarding insertion of implants following training.

## Methods

### Study Site

The evaluation will be conducted in 3 pilot districts in the regions of East (Namutumba), North (Lira Municipality), and South (Kyotera) (Figure 1). These districts were selected because training and certification of the CHEWs have been completed and the electronic Community Health Information System has been rolled out.

**Figure 1. F1:**
[figure not shown]
A map of Uganda showing the districts included in the community-based implant project.

### Study Design

The evaluation will use a convergent parallel mixed-method cross-sectional design using both quantitative and qualitative methods. The quantitative component will use a noninferiority design [14]. This involves a comparison of the competence of the currently authorized cadre to offer the service to the proposed cadre (CHEWs). The noninferior design is methodologically more rigorous than pre-post designs that have been used for assessments in previous studies [10,11].

The qualitative component will use the descriptive qualitative study approach. The descriptive qualitative study approach is an emerging approach that has been used in health care research to understand or identify participants’ experiences and perceptions [15] of the intervention or why the intervention worked or did not work and how the intervention might be improved [16].

### Study Population

The study population will include trained CHEWs, clients, health workers, program managers, and policymakers.

### Inclusion Criteria

The evaluation will include CHEWs who were trained and engaged in implant insertion as well as health workers who were engaged in the intervention as either trainers or supervisors of the CHEWs. Health workers engaged in the provision of long-term reversible family planning or those at the policy level at the national and district levels will also be included. The evaluation will also include clients defined as women of reproductive age who have obtained family planning services provided by CHEWs. To obtain perspectives from spouses of family planning users, men who are aged ≥18 years and in a relationship or union with a woman will also be included in the evaluation.

### Exclusion Criteria

Critically ill clients or those deemed unable to answer questions due to living with cognitive disabilities will be excluded. All potential respondents who refuse to respond or do not consent, or those who will not be available during the duration of the study, will be excluded.

### Sample Size Estimation

#### Quantitative Data

##### Sample Size Estimation: Noninferiority Design

CHEWs will be assessed on their competency to insert implants, under some domains with corresponding items, following training in the selected districts. The assessment of the competency of the CHEWs will be compared to the competency of the qualified health facility providers in the cadre currently authorized to insert implants. Competency will be measured on a continuous scale and summarized as mean (SD) scores. The competency of CHEWs should not be *worse than* that of the authorized cadre, within a margin of acceptable difference (-*d*_*NI*_), accounting for the mean (SD) score competency of authorized cadres (*μ*_*B*_) and that of CHEWs (*μ*_*A*_), and a 1-sided test.

We assumed an SD (*σ*^2^) of the competency scores, and the noninferiority limit (-*d*_*NI*_) was set at −10. At a power of 90% and 1-sided 95% CI, this resulted in a total of 138 participants (69, 50%, cadres authorized to provide implants and 69, 50%, CHEWs) needed to demonstrate that there is truly no difference between the competency of the cadres authorized and the trained CHEWs. We adjusted for a nonresponse rate of 10% and a design effect of 1.2 because multiple CHEWs selected from similar settings and cadres authorized selected from the same health facilities observations will be correlated. This adjustment will result in a minimum of (138×1.2)/0.9=184 (92 CHEWs and 92 authorized cadres).

Compared with a randomized trial, the noninferiority design is more appropriate for this evaluation because it would be a false assumption to randomize participants to receive the service by the CHEWs or the authorized cadre because the 2 groups are not comparable in terms of level of training and competencies. The authorized cadre has gone through formal training, which is not comparable with the training the CHEWs have received; therefore, the best approach for any comparison is such that the competencies of the CHEWs are noninferior or at most equal to the competencies of the authorized cadre.

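### The sample-size paragraph names "no difference" as what 138 participants will demonstrate at 90% power, but the one-sided noninferiority calculation can only show that CHEWs are not worse by 10 points or more

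*Protocol article*

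**What the plan says.** All of this is in the protocol article, Methods, under Sample Size Estimation: Noninferiority Design.

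- The aim is stated in noninferiority terms: "The competency of CHEWs should not be *worse than* that of the authorized cadre, within a margin of acceptable difference", "and a 1-sided test", with the limit set at −10.
- The size follows: "At a power of 90% and 1-sided 95% CI, this resulted in a total of 138 participants", split equally as 69 authorized providers and 69 CHEWs.
- The same sentence then gives the purpose of those 138 participants: they are "needed to demonstrate that there is truly no difference between the competency of the cadres authorized and the trained CHEWs".
- On variability the text reads "We assumed an SD (*σ*^2^) of the competency scores" and prints no value. It does not state a true difference as a planning assumption.
- The inflation is given as "We adjusted for a nonresponse rate of 10% and a design effect of 1.2", leading to 184 (92 per group).

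**The concern.** One paragraph attaches two different claims to one sample size. The first, that CHEWs are not worse by more than a margin, is what a one-sided comparison against −10 tests. The second, that the cadres do not differ, is something this test cannot conclude. The usual planning statement makes equality the condition for the power; here it has become the finding.

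What is at stake is what the study may claim. A successful result is compatible with a CHEW deficit of anything short of 10 points, and a one-sided limit places no upper bound on the difference. A reader who follows the sentence could report that result as demonstrated equal competence. The slip has company in the article. The Quantitative Data Analysis section illustrates its methods with a chi-square test whose null is equal task proportions. The Anticipated Implications section expects CHEW competence to show no significant difference from the authorized cadre. A nonsignificant difference is not evidence of noninferiority, so the sample-size paragraph should state the claim exactly.

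**Working it through.** **Inputs printed in the article:** limit −10; one-sided 95% confidence interval, so one-sided alpha 0.05 (z = 1.6449); power 90% (z = 1.2816); equal groups; design effect 1.2; nonresponse 10%.

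**Inputs not printed:** the SD, and the true difference d (CHEW minus authorized cadre) at which the 90% is calculated.

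**Step 1. Reproduce the plan's figure.** For noninferiority of two means,

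n per group = 2 × (1.6449 + 1.2816)² × SD² / (10 + d)².

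Assume d = 0 and SD = 20: 2 × 8.564 × 400 / 100 = 68.51, rounded up to 69 per group, 138 in total. With d = 0, the SDs that round up to 69 run from about 19.93 to 20.07. Inflation: 138 × 1.2 / 0.9 = 184. Both printed totals are reproduced.

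**Step 2. What N does and does not identify.** The formula depends on the SD and d only through the ratio SD / (10 + d). Any pair with ratio 2 gives the same 68.51:

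| Assumed SD | Assumed d | SD / (10 + d) | n per group |
|---|---|---|---|
| 20 | 0 | 20/10 = 2 | 68.51 → 69 |
| 18 | −1 | 18/9 = 2 | 68.51 → 69 |
| 16 | −2 | 16/8 = 2 | 68.51 → 69 |

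So 138 is consistent with a zero true difference, but does not prove that zero was used.

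**Step 3. What success means.** Success requires: observed difference − 1.6449 × SE > −10. At the planned size, (10 + d) = 2.9264 × SE.

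- If d = 0 was assumed: SE = 10 / 2.9264 = 3.417, and success needs an observed difference above −10 + 1.6449 × 3.417 = −4.4.
- If d = −2 was assumed: SE = 8 / 2.9264 = 2.734, and success needs an observed difference above −10 + 1.6449 × 2.734 = −5.5.

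Under either assumption the study can succeed with CHEWs scoring several points lower on average.

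**Step 4. Set the two claims side by side.** The test rejects the hypothesis that CHEWs are worse by 10 points or more. Rejection supports a difference greater than −10 and nothing narrower. Equality of means is a single point inside that region, and no finite sample can demonstrate it. The 90% is the probability of rejection at an assumed true difference. It is not the probability of establishing that difference.

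**The case against.** The strongest defence is that this is one loose clause in a paragraph that is otherwise right. The heading, the margin, the one-sided test and the one-sided interval all say noninferiority, as do the Abstract and the Study Design section. No equivalence test or equivalence decision rule appears anywhere. The arithmetic is sound, and no data item, margin or sample changes. All of that stands, and it limits the point to wording. It does not remove it, because the clause is the article's explicit statement of what its sample size will show, and that statement is wrong.

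A reader might infer more, but the documents do not support these readings:

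- **That the power for a no-difference claim falls short by a known amount.** With an assumed SD of 20 and assumed limits of ±10, two one-sided tests at 69 per group would have 80.4% power at zero difference. At SD 18 the figure is 89.4% and at SD 16 it is 95.7%, above the printed 90%. The article gives neither the SD nor an upper limit, and it proposes no such test.
- **That noninferiority power drops to stated levels for a small CHEW deficit.** Any such figure depends on the SD. If the plan used SD 16 with a true difference of −2, the power at −2 is already about 90%.
- **That the article conceals an assumption of zero difference.** If zero was assumed, the words are there in the same sentence, only in the wrong role.
- **That the article itself predicts lower CHEW scores.** Its remark that the cadres are not comparable belongs to the argument against randomizing. It is not a planning estimate of a deficit.

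**Conclusion.** The point holds as an error in what the 90% power is said to apply to. The calculation is for one-sided noninferiority at −10. Its success shows that the CHEW mean is not worse by 10 points or more, and it shows neither absence of a difference nor equal competence. This conclusion needs no assumption about the SD.

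The totals of 138 and 184 are consistent with noninferiority and should stay. The SD of about 20 is implied only if the true difference was taken as zero. Because neither is printed, no numerical shortfall in power can be attached to this point. The consequence is confined to the claim the study may make, which a one-sentence correction settles.

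**What to change.** Replace the sentence with wording such as:

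*If the true mean difference between the cadres is zero, 138 participants (69 per group) give 90% power that the lower limit of the one-sided 95% CI for the mean difference (CHEW minus authorized cadre) lies above −10.*

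The sponsor should confirm that zero was the difference assumed, and print its own value if it was not. Add one line saying that success supports a conclusion of not worse by 10 points or more, and does not support a conclusion of no difference or equal competence.

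Do not insert power values that rest on a back-solved SD. If the sponsor chooses to report power under a small CHEW deficit, it should use the SD it actually assumed.

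The cost is wording only, with N unchanged at 138 (184 inflated). The downside is a more modest stated claim.

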### Data Collection Methods

#### Quantitative Data Collection

The quantitative data will be collected through observations among CHEWs and authorized cadres inserting implants as part of the noninferiority assessment. The observation data will be collected using an observation checklist that was developed based on the implant insertion curriculum. The observation data will be used to quantitatively assess competence during the insertion of implants.

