### Strengths and Limitations

This study has several strengths and limitations. The study applies a noninferior design, which is methodologically more rigorous compared with pre-post designs that have been used for assessment in previous studies [10,11]. In addition, the study uses a convergent parallel mixed methods design, which allows for the collection of both quantitative and qualitative data to reinforce each other. The limitations are the risk of clustering of observations around factors such as the district, the health facility where observations are made, and the observers making the observations. However, we will adjust for clustering in the quantitative analysis.

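### Noninferiority is offered as an alternative to randomization, and nothing described makes the two cadres' observed insertions like-for-like, so procedure or client mix could bias the score difference in either direction

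*Protocol article*

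**What the plan says.** The Methods paragraph of the abstract states: "Compared with a randomized controlled trial, the noninferiority design is more appropriate for this evaluation". The section Sample Size Estimation: Noninferiority Design repeats the argument, saying that "it would be a false assumption to randomize participants to receive the service by the CHEWs or the authorized cadre", and gives the reason: "because the 2 groups are not comparable in terms of level of training and competencies". Study Design describes the overall structure: "The evaluation will use a convergent parallel mixed-method cross-sectional design using both quantitative and qualitative methods". Strengths and Limitations adds: "The study applies a noninferior design, which is methodologically more rigorous compared with pre-post designs".

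On what is observed:
- Community-Based Implant Provision Project says that CHEWs were trained to "provide Implanon NXT (Organon Pharma Limited) insertion as well as appropriate referral for implant removal".
- Quantitative Data Collection describes the data as "observations among CHEWs and authorized cadres inserting implants", scored on a checklist derived from the insertion curriculum. It states no product or procedure for the authorized cadre.
- Sampling Procedure draws providers at random within cadre. It allows authorized providers to come from neighboring districts when there are too few, on the ground that their competence should not depend on place.
- Competencies of the CHEWs to Insert Implants specifies one observed procedure per CHEW.
- Quantitative Data Analysis names observer, facility and district as factors to control, as sources of dependence or clustering. The limitations paragraph names clustering only.

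**The concern.** The design argument sets two things against each other that are not alternatives. Randomization is a way of assigning clients (or procedures) to providers. Noninferiority is a choice of hypothesis and margin, and a noninferiority comparison can be randomized or not. The reason given does not help: a cadre's training cannot be randomized, but it is the thing being compared. Allocating clients between cadres would balance the clients and would not require the providers to be alike.

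Because noninferiority is presented as the answer to the comparability problem, the article does not go on to ask what else differs between the two sets of observed insertions. If one cadre's observed clients or procedures tend to score lower on the checklist for reasons unrelated to skill, the mean difference carries that imbalance. The result is meant to inform scale-up, so an error in either direction matters: declaring noninferiority when CHEWs are at the limit, or failing to show it when the cadres are equal.

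**Working it through.** **Is the comparison protected against mix differences?** Taking each safeguard in turn:
- Random sampling of providers makes each cadre's sample represent that cadre. It does not balance clients or procedures between cadres.
- A common checklist standardizes the scoring, not the case being scored.
- Control for observer, facility and district addresses clustering and differences between places. It does not address differences in client or procedure within a place. A neighboring district that supplies only authorized providers contains no CHEW to compare with, so adjustment for district cannot correct an imbalance arising there.
- Nothing described allocates, matches or restricts the clients or procedures observed.

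**The plan's own figure.** Inputs from the sample size section: limit −10 (taken here as points on the competency score), true difference 0, one-sided 5%, power 90%. The SD is not stated, so it is an assumption.
- n per group = 2 × (1.645 + 1.282)² × SD² / 10². With SD 20 this is 68.5, rounded up to 69, or 138 in total. Solving back from 69 gives SD 20.07. An SD of 15 would give 39 per group and an SD of 25 would give 108.
- Inflation: 138 × 1.2 / 0.9 = 184, or 92 per group. This is reproduced exactly. Conversely, 92 × 0.9 / 1.2 = 69 effective per group.

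**Illustration of bias.** Let b be the number of points by which mix favors CHEWs. The documents give no value for b.
- SE = 20 × √(2/69) = 3.405.
- At a true difference of −10, P(declare noninferiority) = Φ(b/SE − 1.645). For b = 3: Φ(0.881 − 1.645) = Φ(−0.764) = 0.22.
- At a true difference of 0 with mix b points against CHEWs, power = Φ((10 − b)/SE − 1.645). For b = 0: Φ(2.937 − 1.645) = 0.90. For b = 5: Φ(1.468 − 1.645) = 0.43.

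Chance of declaring noninferiority when CHEWs are truly at the limit:

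| b (points favoring CHEWs) | SD 15 | SD 20 | SD 25 |
|---|---|---|---|
| 0 | 5% | 5% | 5% |
| 2 | 19.4% | 14.5% | 12.0% |
| 3 | 31.9% | 22.2% | 17.4% |
| 5 | 62.3% | 43.0% | 31.9% |

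Power with no true difference, with no imbalance and then with 5 points against CHEWs: 98.8% to 62.3% (SD 15), 90.2% to 43.0% (SD 20), 76.0% to 31.9% (SD 25).

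A larger sample does not remove b. It only makes the biased estimate more precise.

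**The case against.** The other side has several good points.

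- A reader might infer that authorized providers will be scored on other products, on removals with reinsertion, or on harder referred cases, and that this makes noninferiority easier to declare. The documents do not say so. They describe insertion for both cadres, on one insertion checklist. Removals are referred to facilities, but nothing says that those visits enter the observed sample. This is a possibility left open, not a documented fact.
- CHEWs were stationed at their supervising facilities, beside the health workers, and served any eligible consenting woman. That suggests a shared client pool and makes a large imbalance less likely, although recruitment from neighboring districts weakens the overlap.
- The outcome is a process score of provider steps, and an omitted step counts as not done only where it was needed. This limits how far case mix can move the score, though it does not rule it out.
- The direction is unknown. Trainers and supervisors of the CHEWs are eligible for the evaluation. If some are in the comparator sample, their familiarity with the curriculum could raise its scores and make noninferiority harder to show.
- The claim of greater rigor is made against pre-post designs, not against randomization, and a concurrent comparator is a fair advantage there. The cross-sectional design is stated openly.
- This is an article. Client selection, checklist fields and model covariates may be in the full protocol or analysis plan, and the list of adjustment factors is open-ended.

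These points limit the size and direction of any bias that can be claimed. They do not repair the stated rationale, which appears twice, or the limitations paragraph, which names clustering and not confounding.

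**Conclusion.** The point holds in a limited form. The argument that noninferiority is more appropriate than a randomized trial is wrong as written. The study is a non-randomized comparison, and the safeguards described do not address procedure or client mix. Mix could therefore bias the score difference, in either direction and by an unknown amount.

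The documents do not support a claim that the bias favors CHEWs, or any single error rate. The illustrative figures (at SD 20, a 5% to 43% chance of declaring noninferiority at the limit for 0 to 5 points favoring CHEWs; power falling from 90% to 43% for 5 points against) rest on assumed imbalances, an SD inferred from the sample size, and 69 effective observations per group. They show only that imbalances well inside the 10-point limit would matter. The correction should be made, and it does not put the study's feasibility in question.

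**What to change.** 1. Delete the argument that noninferiority is more appropriate than a randomized trial, in the abstract and in the sample size section. Describe the study as a non-randomized cross-sectional comparison with a noninferiority hypothesis.
2. In both cadres, score only Implanon NXT insertions without a removal, on the next eligible consenting client.
3. Record product and client type (first-time or repeat implant user; referred or not) on the electronic checklist, and adjust for client type in the primary comparison of mean scores.
4. Name residual confounding by client and procedure mix as a limitation, beside clustering.

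Cost: items 1 and 4 are wording, and item 3 is a few fields. Item 2 leaves some authorized-cadre procedures unscored, so observers may wait longer, and the article already foresees a shortage of authorized providers in some districts. The abstract reports that data collection had started by August 2025, so earlier observations may lack these fields. For those, apply the restriction and adjustment where product and client type can be recovered, and report a sensitivity analysis to show whether the conclusion depends on the rest.
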